# Hospital-based interventional two-arm parallel comparative study on dydrogesterone vs combined oral contraceptive pills for functional ovarian cysts

**DOI:** 10.12688/f1000research.142012.1

**Published:** 2024-01-25

**Keywords:** Functional ovarian cysts, Combined oral contraceptive pills, Dydrogesterone, Reproductive-age women, Efficacy, Safety

## Abstract

**Background:**

Functional ovarian cysts are common among women of reproductive age, often necessitating medical intervention. This hospital-based interventional study compares the efficacy and safety of combined oral contraceptive pills (COC) and dydrogesterone in managing functional ovarian cysts.

**Methods:**

This randomized controlled trial will be conducted over two years at the Department of Obstetrics & Gynecology, AVBRH, Datta Meghe Institute of Medical Sciences. The study population consists of reproductive-age women seeking care at the outpatient unit of Obstetrics and Gynecology at AVBRH hospital. The sample size of 46 participants per group has been calculated based on a 95% confidence interval and the estimated prevalence of functional ovarian cysts. Group A will receive low-dose COC for three menstrual cycles. At the same time, Group B will be administered dydrogesterone (10 mg twice daily) for ten days during the luteal phase, repeated across three cycles.

**Expected outcomes:**

The primary outcomes include evaluating the recession of cysts within three months, monitoring alterations in menstrual patterns (frequency, regularity, duration, and volume), assessing the necessary treatment duration, and observing potential side effects (e.g., nausea, vomiting, weight gain, and acne) and complications (e.g., thromboembolism, delayed menstrual cycles post-treatment, and interactions with other drugs). Data analysis will encompass descriptive statistics, comparative tests, and regression models to assess the primary outcomes. The significance level for hypothesis testing will be 0.05 with a two-tailed approach.

**Registration:**

CTRI/2023/04/051811.

## Introduction

Functional ovarian cysts, a prevalent occurrence among women of reproductive age, frequently require medical intervention due to their potential to disrupt fertility and overall health. These cysts originate from the intricate interplay of normal physiological processes involved in ovulation and follicular development.
^
1
^ However, in certain instances, deviations from this intricate balance can lead to the development of cysts that warrant medical attention. Such deviations can manifest as variations in size, persistence, or symptomatic expression, prompting clinical intervention to prevent complications and alleviate patient discomfort.

The management landscape for functional ovarian cysts comprises a spectrum of approaches, encompassing both surgical and medical modalities. Surgical interventions, while effective, often involve inherent risks and potential disruptions to reproductive function. On the other hand, medical options promise to preserve fertility and avoid invasive procedures. Despite the existing armamentarium, pursuing treatments that balance efficacy and safety remains an ongoing endeavor.
^
2
^
^,^
^
3
^

This study seeks to address this need by conducting a hospital-based interventional two-arm parallel comparative investigation to compare the effectiveness and safety of two distinct medical interventions – combined oral contraceptive pills (COC) and dydrogesterone. COC, renowned for their hormonal regulatory effects, have demonstrated potential in mitigating cystic growth. Conversely, dydrogesterone, a synthetic progestin, presents an alternative therapeutic avenue with its luteal phase support capabilities.
^
4
^

The primary objective is to evaluate the efficacy of these interventions in terms of cyst regression and their influence on the menstrual pattern. Additionally, the study will focus on assessing the safety profile, including potential side effects, treatment duration, and the occurrence of complications. The outcomes of this research will contribute essential insights to inform clinical decision-making, guide treatment strategies, and optimize patient care. By comparing the outcomes of these interventions in a controlled and systematic manner, this study advances our understanding of medical management approaches for functional ovarian cysts, ultimately enhancing the quality of care for women facing this common medical concern.

### Aim

To compare the effectiveness and safety of combined oral contraceptive pills (COC) and dydrogesterone for the medical management of functional ovarian cysts.

### Objectives

1.To study the effectiveness and safety of combined oral contraceptive pills in treating functional ovarian cysts.2.To study the effectiveness and safety of dydrogesterone in treating functional ovarian cysts.3.To compare the effectiveness and safety between combined oral contraceptive pills and dydrogesterone.

## Protocol

### Study design

This research employs a randomized controlled trial methodology, falling within the category of interventional studies. The study is planned to span a duration of 2 years. The study will be conducted at the Department of Obstetrics & Gynecology, AVBRH, Datta Meghe Institute of Medical Sciences, in Sawangi (Meghe), Wardha.

### Participants

The study will focus on women of reproductive age seeking medical attention at the outpatient unit of Obstetrics and Gynecology within AVBRH hospital. These participants will be selected based on their fulfillment of the defined inclusion and exclusion criteria.

### Inclusion criteria

Participants within the reproductive age range of 18 to 44 years, possessing ovarian cysts between 3 to 10 centimeters with a single compartment and precise contents, and having a body mass index (BMI) within the range of 18.5 to 29.9 will be considered for inclusion.

### Exclusion criteria

Prospective participants with dermoid cysts, endometriosis, malignancies, ruptured cysts, cyst torsion, recent use of hormonal medications, history of ovarian cyst removal (cystectomy), and specific medical conditions will be excluded from the study.

### Allocation

The eligible participants will be assigned randomly to two study groups utilizing a 1:1 allocation ratio. The random allocation will be achieved by applying the sealed envelope technique.

### Interventions

Participants in Group A will receive a course of ethinyl estradiol (0.03 mg) + Levonorgestrel (0.15 mg) combined oral contraceptive pills over three menstrual cycles. In Group B, participants will be administered dydrogesterone, with 10 mg taken twice daily for ten days during the luteal phase. This protocol will be repeated across three consecutive menstrual cycles.

Criteria for discontinuing or modifying allocated interventions will be clearly defined in our study. These criteria may include, but are not limited to, the development of severe adverse events, non-compliance with the treatment protocols, or the emergence of conditions that contraindicate further participation. In such cases, the participant will be withdrawn from the study, and the reasons for discontinuation or modification will be documented.

To ensure participant adherence to allocated interventions, we will implement the following strategies:
•Regular follow-up appointments and reminders to participants regarding treatment regimens.•Monitoring of participant compliance through self-reporting and pill counts for both intervention groups.•Tracking participant satisfaction and addressing any concerns or issues that may affect adherence.•Continuous communication between the research team and participants to address any questions or issues related to the interventions.

Participants will be advised to avoid the use of other hormonal medications or treatments during the study period, as these may confound the results. However, the use of non-hormonal over-the-counter medications will be allowed as needed, and these instances will be recorded.

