### Allocation

The allocation sequence will be generated by a biostatistician, who is not directly involved in the enrolment process. The enrolment of participants will be conducted by clinical research coordinators, while the assignment of participants to interventions will be performed by a research pharmacist based on the allocation sequence. Due to the nature of the interventions, participants cannot be blinded. However, outcome assessors and data analysts will be blinded to the treatment assignments. Unblinding may be considered in the event of a medical emergency or if knowledge of the treatment assignment is deemed necessary for the safety and well-being of the participant. Unblinding will only occur when the unblinded status is required for clinical management.

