### Primary outcome measures

**Effectiveness assessment:**
1.
**Regression of cysts:** To monitor the regression of ovarian cysts, we will conduct regular ultrasound evaluations. Participants from both study groups will undergo ultrasound assessments after each menstrual cycle. These assessments will continue until either the cysts dissipate or for a maximum duration of three months.2.
**Menstrual pattern changes:** To observe shifts in menstrual patterns, we will have participants maintain menstrual diaries. Participants will record information regarding the frequency, regularity, duration, and volume of their menstrual cycles. Data will be collected at each follow-up appointment, allowing us to track any changes over time.

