### Sample size

Formula using mean difference

$$n1=n2=2\frac{{\left(Z_{\alpha }+Z_{\beta }\right)}^{2}\sigma^{2}}{{\left(\delta \right)}^{2}}$$

$$Z_{\alpha }=1.96$$

α=Type I error at 5% at both sides two tailed

$$Z_{\beta }=1.28=\text{Power at 90\%}$$

Dydrogesterone vs combined oral contraceptive pills for functional ovarian cysts (δ) = 0.3

Considering 30% superiority = (0.3*30)/100 = 0.09

Standard deviation = 1

Minimum sample size N =

$n1=n2=2\frac{{\left(1.96+0.09\right)}^{2}{\left(\;1\right)}^{2}}{{\left(0.09\right)}^{2}}=42\;\text{per group}$

Considering 10% drop out = 4

Total sample size required = 42 + 4 = 46 per group. Reference study.
^
5
^

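### Stopping or modifying treatment takes a woman out of the study, so her remaining outcomes go uncollected and the arm comparison can be biased

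*Protocol article*

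**What the plan says.** The rule is in the protocol article, Interventions. The paragraph is about criteria for stopping or changing the allocated treatment. It introduces them loosely ("These criteria may include, but are not limited to") and names three: "the development of severe adverse events, non-compliance with the treatment protocols, or the emergence of conditions that contraindicate further participation". The consequence is stated without a hedge: "In such cases, the participant will be withdrawn from the study, and the reasons for discontinuation or modification will be documented". The trigger is something that happens to the treatment; the consequence is exit from the study. Read literally, this covers even a woman whose treatment is only modified.

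Other sections bear on it:

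- **Detection of non-compliance** (Interventions): "Monitoring of participant compliance through self-reporting and pill counts for both intervention groups".
- **Regimens** (Interventions): Group A takes a pill course over three cycles. Group B takes dydrogesterone, "10 mg taken twice daily for ten days during the luteal phase", in each of three cycles.
- **Blinding** (Allocation): "Due to the nature of the interventions, participants cannot be blinded". Outcome assessors and data analysts are blinded.
- **Ultrasound schedule** (Effectiveness assessment): one scan after each cycle, and "These assessments will continue until either the cysts dissipate or for a maximum duration of three months". Nothing is said about women who have been withdrawn.
- **Safety outcomes** (Safety assessment): these are listed among the primary outcomes. They include liver tests, thromboembolism and late return of menses once treatment has ended.

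**The concern.** A randomised comparison is protected only while the women compared are those who were randomised. Here the reasons for leaving arise after randomisation and can depend on the assigned drug. The two schedules differ, each woman knows which she is on, and non-compliance is judged partly from her own report. Blinded assessors do not help, because the selection happens before there is a scan to read.

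If withdrawal, or the outlook of those withdrawn, differs between arms, the women with a three-month result are no longer comparable groups, and a difference in cyst regression can appear where none exists. Safety is affected too. Late return of menses can be seen only after treatment stops, so a woman who leaves the study on stopping cannot contribute it, and her remaining liver tests and complication checks also end. On this point the Interventions and Safety assessment sections pull against each other and need to be reconciled.

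**Working it through.** **1. Does any section keep these women in follow-up?** Interventions takes them out. Effectiveness assessment and the later Follow-up section schedule scans but make no provision after withdrawal. The earlier Follow-up section promotes retention in general terms and does not override the rule. Statistical analysis names tests for cyst regression but does not deal with withdrawn women. So nothing shown restores their outcomes.

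**2. How large could the bias be?** The protocol gives no resolution or withdrawal rate, so there is no figure of its own to reproduce. The rates below are assumptions; only the 46 per arm comes from the protocol (Sample size).

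- p = true resolution among all randomised women, 0.60 in both arms (no true difference)
- w = share withdrawn: 0.15 vs 0.05, or 0.20 vs 0.05 (at 46 per arm, 6.9 vs 2.3 or 9.2 vs 2.3 women)
- r = resolution among withdrawn women: 0.20 to 0.40
- no outcome is recorded for any withdrawn woman

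Resolution among those remaining: c = (p − w·r)/(1 − w).

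| r | c at w = 0.20 | c at w = 0.15 | c at w = 0.05 | 0.15 vs 0.05 | 0.20 vs 0.05 |
|---|---|---|---|---|---|
| 0.20 | 0.56/0.80 = 0.700 | 0.57/0.85 = 0.671 | 0.59/0.95 = 0.621 | 0.050 | 0.079 |
| 0.30 | 0.54/0.80 = 0.675 | 0.555/0.85 = 0.653 | 0.585/0.95 = 0.616 | 0.037 | 0.059 |
| 0.40 | 0.52/0.80 = 0.650 | 0.54/0.85 = 0.635 | 0.58/0.95 = 0.611 | 0.025 | 0.039 |

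The spurious difference is 2.5–5.0 points in the first scenario and 3.9–7.9 in the second.

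**3. Yardstick.** The standard error of the difference at 60% resolution and 46 per arm is √(2 × 0.60 × 0.40/46) = √0.01043 = 0.102, about 10 points. The bias is roughly a quarter to a half of one standard error in the first scenario and 0.4 to 0.8 in the second.

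**4. When does it vanish or reverse?** Each arm is shifted by c − p = w(p − r)/(1 − w).

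- Equal w and equal r in both arms: the shifts cancel and the bias is zero.
- r = p: no shift in either arm.
- r > p: the sign reverses. With r = 0.80 and 15% vs 5%, 0.48/0.85 − 0.56/0.95 = 0.565 − 0.589 = −0.025.

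**5. Effect on the test.** A simulation of the two-proportion chi-square test (46 per arm, 20,000 runs, true resolution 70% in both arms, withdrawn women left out) gave these rejection rates at a nominal 5%:

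- 15% vs 5% withdrawn, 30% of them resolving: 7.9% (spurious difference 5.0 points)
- 15% vs 5% withdrawn, none resolving: 15.6% (8.7 points)
- 10% in both arms, none resolving: 4.7%
- everyone followed and analysed, all scenarios run: 4.6–5.2%

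**6. Does counting missing scans as not resolved repair it?** Each arm's rate becomes p − w·r. For 15% vs 5% the difference is 0.57 − 0.59 = −0.02 at r = 0.20 and 0.54 − 0.58 = −0.04 at r = 0.40. For 20% vs 5% it is −0.03 and −0.06. That rule has its own bias, in the opposite direction. In the 15% vs 5% case at r = 0.40 it exceeds the bias it replaces (4 points against 2.5).

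**The case against.** The strongest reply is that the sentence may be loose wording. Removing a woman from the study because her treatment was merely modified makes little sense, so the authors may have meant leaving treatment. That is possible, but the text says the study, and staff who follow it would stop the scans. The ambiguity is a reason to reword it.

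A second reply is that the analysis set and missing-data rules are commonly left to a statistical analysis plan. That is right, and their absence is not the point here. A later plan can choose a set or impute, but it cannot supply scans that the protocol has told staff not to take.

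Other objections stand and limit the point:

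- Scans follow every cycle, so a woman whose cyst has gone before she is withdrawn already has her result, and others will have interim scans. A reader might infer that outcomes exist only for compliant women who tolerate treatment; the schedule does not support that. The illustration leaves out all withdrawn women and so tends to overstate the loss.
- The event that triggers withdrawal is still captured: reasons are documented (Interventions), and adverse events are recorded and assessed (Adverse events and unintended effects). Only later safety follow-up is lost.
- A reader might infer that the drug with more withdrawals must look better. That requires withdrawn women to resolve less often than the rest, which the protocol does not say.
- A reader might set the bias against the 0.09 in Sample size as though it were nine percentage points. There it is a mean difference used with a standard deviation of 1, so the units do not match.
- A reader might take the allowance "Considering 10% drop out = 4" to be these women. Sample size does not link it to the withdrawal rule.

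**Conclusion.** The concern holds as a stated rule that can bias the randomised comparison of cyst regression and that shortens safety follow-up. It rests on the text of Interventions and on the absence of any section that continues assessment after withdrawal. That bias will occur is not established: it needs withdrawal, or the prognosis of withdrawn women, to differ by arm. Different regimens and unblinded participants make this plausible but do not show it.

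Under the assumed rates the spurious difference is 2.5–7.9 points across the two scenarios, smaller than one standard error at the planned size. Size and direction rest wholly on assumptions. The case for changing the rule before enrolment is that uncollected scans cannot be recovered at analysis, while collecting them needs no new visits.

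**What to change.** Reword the sentence in Interventions so that stopping or modifying the allocated treatment does not end study participation. The ultrasound, diary and safety assessments already scheduled continue to three months unless the woman withdraws consent or continued assessment is not possible. Leave the clinical criteria for stopping treatment as they are; only the consequence for follow-up changes.

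Add one analysis sentence: all randomised women are analysed in their allocated arm, with sensitivity analyses for scans still missing that cover more than one assumption. Counting missing as not resolved should not be the only one, since it is biased when missingness differs by arm.

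The cost is two sentences. The visits are already planned, and Study status says the trial has not begun. The downside is some dilution of the estimate by non-adherence.

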### Enrolment

We will employ several strategies to achieve adequate participant enrolment:
•Collaboration with healthcare providers in the Department of Obstetrics & Gynecology, AVBRH, to facilitate referrals and patient recruitment.•Public awareness campaigns and information dissemination about the study in the hospital’s outpatient unit.•Ensuring that the inclusion and exclusion criteria are clear and well-communicated to potential participants.

### Allocation

The allocation sequence will be generated by a biostatistician, who is not directly involved in the enrolment process. The enrolment of participants will be conducted by clinical research coordinators, while the assignment of participants to interventions will be performed by a research pharmacist based on the allocation sequence. Due to the nature of the interventions, participants cannot be blinded. However, outcome assessors and data analysts will be blinded to the treatment assignments. Unblinding may be considered in the event of a medical emergency or if knowledge of the treatment assignment is deemed necessary for the safety and well-being of the participant. Unblinding will only occur when the unblinded status is required for clinical management.

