### Adverse events and unintended effects

We will implement systematic procedures for collecting, assessing, reporting, and managing adverse events. Adverse events will be documented by the clinical research team, assessed for causality and severity, and reported to the appropriate regulatory authorities as per regulatory requirements.

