**Safety assessment:**
1.
**Duration of treatment:** We will determine the duration of treatment necessary for each participant by monitoring their response and progress during follow-up appointments. The treatment duration will be based on individual responses and the predefined treatment protocol.2.
**Monitoring side effects:** Participants will be encouraged to report any potential side effects during regular follow-up appointments and will also have access to a dedicated contact point for immediate reporting. Adverse events, including nausea, vomiting, weight gain, and acne, will be documented and assessed for severity and causality.3.
**Effects on liver function tests:** We will conduct regular blood tests to assess liver function. Liver function tests, including alanine aminotransferase (ALT) and aspartate aminotransferase (AST) levels, will be measured at specific intervals during the study. Any abnormal results will be monitored closely.4.
**Tracking critical complications:** We will monitor for critical complications such as thromboembolism, delayed menstrual cycles post-treatment, and potential interactions with other drugs through continuous review of participants’ medical records and regular assessments during follow-up appointments. In the event of a critical complication, immediate actions will be taken following our predefined clinical management plan.

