**Primary outcome measures:** The primary outcomes, centered around effectiveness and safety, encompass the regression of cysts, alterations in menstrual patterns, treatment duration, side effects, and complications. These outcomes holistically capture the impact of the interventions on both the physical and overall well-being of participants. Monitoring cyst regression and menstrual pattern changes offers insights into the interventions’ therapeutic effects, while evaluating safety profiles contributes to a comprehensive understanding of potential risks.

**Implications and future directions:** The findings of this study have far-reaching implications for clinical practice. The data generated from the study will aid clinicians in making informed treatment decisions, balancing effectiveness and safety considerations. Furthermore, this research sets the stage for more targeted investigations into the mechanisms of action of COC and dydrogesterone, potentially uncovering novel insights into the pathophysiology of functional ovarian cysts.

**Limitations and considerations:** It’s important to acknowledge potential limitations, such as the limited follow-up duration and the exclusive focus on two treatment options. Future studies could explore the effects of alternative interventions and longer-term outcomes, providing a more comprehensive understanding of functional ovarian cyst management.

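### Blinded outcome assessment is claimed without limit, but two primary outcomes, menstrual pattern and side effects, are reported by unblinded women and are therefore open-label

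*Protocol article*

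**What the plan says.** The second Allocation section of the protocol article makes two statements in sequence. The first is "Due to the nature of the interventions, participants cannot be blinded". The next is "However, outcome assessors and data analysts will be blinded to the treatment assignments". The second is not restricted to particular outcomes.

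The Primary outcome measures section, including its safety part, lists six outcomes. For cyst regression, "we will conduct regular ultrasound evaluations". For menstrual pattern, "we will have participants maintain menstrual diaries". For treatment duration, "We will determine the duration of treatment necessary for each participant by monitoring their response and progress during follow-up appointments". Side effects (nausea, vomiting, acne and weight gain are the examples) are collected by encouraging women to report them at follow-up, with a contact point for urgent reports. Liver enzymes are measured from blood. Critical complications are tracked by record review and assessments at follow-up.

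The Discussion confirms the primary status of most of these: "The primary outcomes, centered around effectiveness and safety, encompass the regression of cysts, alterations in menstrual patterns, treatment duration, side effects, and complications".

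On handling of events, Adverse events and unintended effects says: "Adverse events will be documented by the clinical research team, assessed for causality and severity". On adherence, Interventions lists: "Monitoring of participant compliance through self-reporting and pill counts for both intervention groups". Neither passage says who grades causality or who counts the pills.

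**The concern.** An assessor's blind protects an outcome only if the assessor, and not the participant, makes the judgement. Where the participant makes it, her knowledge of treatment is already in the data before any study staff see it. Here she knows whether she takes a contraceptive pill over three cycles or a ten-day luteal course in each cycle, and that knowledge can affect what she notices, records and mentions.

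Both affected outcomes are labelled primary. Side effects also carry much of the trial's safety comparison, which is half of its stated aim. If the Allocation statement stands as worded, a difference in bleeding pattern or symptoms could be reported, and read, as evidence from blinded assessment when it is not.

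The method of collecting side effects adds to this. Reporting that is encouraged but voluntary lets the threshold for mentioning a symptom differ between two groups who know what they are taking.

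**Working it through.** No figure in the document bears on this point, so the check sets the blinding statement beside each outcome. For each one, the question is who generates the observation and who judges it.

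| Outcome (Primary outcome measures) | Where the observation comes from | Consistent with the stated blind? |
|---|---|---|
| Cyst regression | Ultrasound after each cycle | Yes, the scan can be read without knowing the arm |
| Menstrual pattern | Diary kept by the participant | No, she is unblinded by the protocol's own statement |
| Treatment duration | Judged from response at follow-up; decision-maker not named | Not described |
| Side effects | Reported by the participant, then documented and graded | No for the report itself; grader not named |
| Liver enzymes | Laboratory measurement | Yes |
| Critical complications | Record review and follow-up assessment; reviewer not named | Not described |

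Count of the six outcomes:
- in conflict with the blinding statement: 2 (menstrual pattern, side effects)
- compatible with it: 2 (ultrasound regression, liver enzymes)
- blinding undescribed: 2 (treatment duration, critical complications)
- check: 2 + 2 + 2 = 6

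The Discussion's list has five outcomes because it leaves out liver tests. On that list the conflict is 2 of 5.

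The conflict follows from two premises that are both in the text. First, the woman is the source of the diary and of the symptom report. Second, she is not blinded. No assumption about staff roles is needed, and a fuller protocol naming those roles would not remove it.

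**The case against.** The strongest reply is that the article is open about the unblinded participants, and that any reader can see that diaries and symptom reports come from them. Nothing in it says those results will be presented as blinded evidence. The main objective effectiveness measure, cyst regression on ultrasound, fits the stated blind. All of this is true and limits the seriousness of the point. It does not make the unqualified sentence correct for the two participant-reported outcomes.

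One listed side effect, weight gain, can be measured objectively. But the section describes side effects as reported by participants and sets no measurement for weight, so this softens the point only for that item.

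A reader might also infer four stronger claims, which the document does not support.
- **That most primary outcomes are unblinded.** This would need treatment duration and complications to be judged by unblinded staff. The text does not say so. Duration may largely follow the scan result, and thromboembolism could be reviewed with the arm masked.
- **That the people who count pills also assess outcomes.** No role is named for pill counts. The Allocation section names only a biostatistician for the sequence, coordinators for enrolment and a pharmacist for assignment.
- **That causality grading must be unblinded.** The grader is not named, and relatedness to study treatment can be graded without knowing the arm.
- **That the ultrasound reader is exposed to the diary or pill count.** Nothing says so. Scan order and access to records are operational details that a condensed article may leave to the full protocol.

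Nor does the document restrict the side-effect comparison to events judged drug-related. The Statistical analysis section compares the incidence of side effects.

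**Conclusion.** The point holds in a limited form. The blinding statement is wrong for 2 of the 6 outcomes under the primary heading: menstrual pattern and side effects. Those comparisons are open-label whoever records the answers. For treatment duration and critical complications, blinding is undescribed and not shown to be absent. For ultrasound regression and liver enzymes, the stated blind is workable.

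The conclusion rests only on the article's own description of who supplies each observation and on its statement that participants are unblinded. The document gives no expected side-effect rate and no information on differential reporting, so neither the size nor the direction of a bias can be stated. The defect does not invalidate the ultrasound endpoint. It misdescribes the quality of evidence for two outcomes that the protocol calls primary.

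**What to change.** Make three changes. According to Study status the trial had not started at publication, so they can be made before enrolment.

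1. In Allocation, limit the statement on blinded assessors to outcomes that participants do not report, naming the ultrasound reading and the laboratory values.
2. State that the menstrual-pattern and side-effect comparisons are open-label and will be interpreted as such.
3. In the side-effects item of the safety assessment, base the between-arm comparison on one fixed symptom checklist. Ask it in the same words at every follow-up visit in both arms, and compare all elicited events. Keep spontaneous reporting and the contact point for safety purposes.

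The checklist does not blind the women. It makes the elicitation the same in both arms, so that a difference depends less on who chose to mention a symptom.

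The cost is a narrower blinding claim, a change of wording and a short form at each visit.
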